**Table 1.0 – Summary of Objectives and Endpoints**

| OBJECTIVES                                                                                                                                                                                                                                                                                                            | CANDIDATE ENDPOINTS                                                                                          | JUSTIFICATION FOR ENDPOINTS                                                                                                                                                                                                                                                                                                                                                                                                           |
|-----------------------------------------------------------------------------------------------------------------------------------------------------------------------------------------------------------------------------------------------------------------------------------------------------------------------|--------------------------------------------------------------------------------------------------------------|---------------------------------------------------------------------------------------------------------------------------------------------------------------------------------------------------------------------------------------------------------------------------------------------------------------------------------------------------------------------------------------------------------------------------------------|
| Primary                                                                                                                                                                                                                                                                                                        |                                                                                                              |                                                                                                                                                                                                                                                                                                                                                                                                                                       |
| To determine if in previously healthy children, who present to an ED with gastroenteritis associated vomiting; is the proportion who develop moderate to severe disease [MVS ≥ 9] following ED evaluation significantly different in those who receive home ondansetron compared to those who receive placebo. | Post-index visit Modified Vesikari Scale (MVS) score in the 7 days following ED disposition  | The MVS is a composite measure which includes several aspects which represent the severity of disease. The score incorporates features of gastroenteritis that are of important to a variety of stakeholders including caregivers, children and physicians (e.g. duration of diarrhea and vomiting, frequency of diarrhea and vomiting, maximal height of fever, the presence of dehydration and the medical interventions required). |
| Secondary                                                                                                                                                                                                                                                                                                      |                                                                                                              |                                                                                                                                                                                                                                                                                                                                                                                                                                       |

**Table 1.0 – Summary of Objectives and Endpoints**

| OBJECTIVES                                                                                                                                                                                                                                                                                                                                                                                                                                                                                                     | CANDIDATE ENDPOINTS                                                                                                                                                                                                                                                                 | JUSTIFICATION FOR ENDPOINTS                                                                                            |
|----------------------------------------------------------------------------------------------------------------------------------------------------------------------------------------------------------------------------------------------------------------------------------------------------------------------------------------------------------------------------------------------------------------------------------------------------------------------------------------------------------------|-------------------------------------------------------------------------------------------------------------------------------------------------------------------------------------------------------------------------------------------------------------------------------------|------------------------------------------------------------------------------------------------------------------------|
| 
Among children receiving active treatment versus placebo:
 
(1) Is there a difference in the (a) duration of vomiting, (b) frequency of vomiting, or (c) the proportion who experience vomiting following ED disposition.
 
(2) Is there a difference in the proportion who require an unscheduled health care provider visit?
 
(3) Is there a difference in the proportion who require intravenous rehydration?
 
(4) Is there a difference in the satisfaction with care?
 | 
1. Vomiting: Frequency, Duration, Proportion
 
2. Health Care Use: ED, Primary Care
 
3. Intravenous rehydration
 
4. Caregiver Satisfaction with Therapy Provided: Likert Scale
                                                                              |                                                                                                                        |
| Safety                                                                                                                                                                                                                                                                                                                                                                                                                                                                                                  |                                                                                                                                                                                                                                                                                     |                                                                                                                        |
| 
To determine if the discharge of children with AGE associated vomiting who are administered ondansetron in the ED with additional doses to be taken at home is associated with adverse events (e.g. diarrhea, revisits) as compared with placebo (i.e. safety).
                                                                                                                                                                                                                                         | 
1. Frequency of diarrheal episodes during the 48-hours following ED disposition.
 
2. Maximal number of diarrheal episodes in 24 hours
 
3. Palpitations
 
4. Syncope/pre-syncope
 
5. Chest Pain
 
6. Arrhythmias
 
7. Serious Adverse Events
 | 
It is crucial to monitor for potential adverse events associated with the introduction of additional therapies.
 |
| Tertiary/Exploratory                                                                                                                                                                                                                                                                                                                                                                                                                                                                                    |                                                                                                                                                                                                                                                                                     |                                                                                                                        |
| None.                                                                                                                                                                                                                                                                                                                                                                                                                                                                                                          | Not applicable                                                                                                                                                                                                                                                                      | Not applicable                                                                                                         |

Following study completion an economic evaluation will be performed.

## 4 STUDY DESIGN

### 4.1 OVERALL DESIGN

We will conduct a Phase III multi-centre, 2-arm, placebo-controlled, double-blind, parallel design randomized controlled trial comparing the effectiveness and adverse event profile of multiple dose (as needed) oral ondansetron compared with placebo when administered to children with acute gastroenteritis (AGE)-associated

vomiting following ED discharge. The study will be stratified by site (6 sites) and weight (< 20kgs and ≥ 20kgs). Weight is being employed, rather than age, as dosing is weight based.

We hypothesize that the administration of ondansetron post-ED discharge will be associated with improved outcomes as compared with placebo.

## 4.2 SCIENTIFIC RATIONALE FOR STUDY DESIGN

There is currently insufficient data to determine with certainty whether additional doses of ondansetron should be administered following the ED disposition of children with vomiting secondary to AGE. While it may be beneficial, studies to date have not provided robust evidence and the potential benefits need to be balanced with the potential to increase the frequency of diarrhea.

## 4.3 JUSTIFICATION FOR DOSE

A standardized dose of 0.15mg/kg of oral ondansetron solution will be used in this study. The maximum singular dose of oral ondansetron provided will be 8mg, and the dose to be administered will be based on the weight of the participant at time of study enrollment. Enough study medication will be provided to enable the administration of a maximum of 6 doses at home. This dosing regimen has been shown to be effective, safe and is within the dosing range (0.13-0.26 mg/kg) that has previously been used for this indication.

A single dose of 8mg has been demonstrated to have a minimal effect on the QTc – prolonging it by only 0.4 msec. Moreover, within the recommended/commonly used dose range of 0.13-0.26 mg/kg, higher doses of ondansetron have not been found to be superior to lower doses.

Children will be administered oral medications as this route has proven to be effective, safe, pragmatic, and easy to use in young children.

Eligible children will receive up to 6 doses of medication [ondansetron oral solution (0.15 mg/kg/dose) or placebo] to be administered every 8 hours at the caregiver's discretion. Such caregiver-driven, after ED discharge dosing protocols are increasingly common with a recent description of a cohort of 996 children among whom 76% received ondansetron in the ED, and 71% were discharged with prescriptions for ondansetron. Moreover the median number of home doses of ondansetron prescribed was 10 (IQR: 6, 12). In this cohort, 7-day ED return rates were similar between groups (6% with prescription, 5% without, P = 0.66). We will have a standardized written handout that the research staff will employ explaining when we suggest that the medication be given.

## 4.4 END OF STUDY DEFINITION

The end of the study is defined as completion of the last visit or procedure shown in the SoA in the trial globally.

A participant is considered to have completed the study if they have completed all phases of the study including the Day 7 email or telephone questionnaire shown in the SoA in Section 1.3. Emergency Department chart review of enrollment/baseline data is performed by study staff at each site and does not involve direct participation by the study participant or caregiver.

It is not necessary for caregivers to administer all study medication doses provided to them to remain compliant with the protocol. Doses are administered based on caregiver assessment of the child's need. The number of

doses administered by the caregiver will be recorded on the follow-up questionnaires completed by email or telephone.

## 5 STUDY POPULATION

### 5.1 INCLUSION CRITERIA

All patients who present to the ED of the six participating institutions will be assessed for eligibility. The screening process will be compliant with each study site's provincial and institutional policies and legislation.

To be eligible to participate in the study, individuals must meet **all** of the following criteria:

1. Provision of signed and dated informed consent and assent (where applicable) forms
2. Stated willingness to comply with all study procedures and availability for the duration of the study.
3. Diagnosis of acute intestinal infectious process confirmed by the treating ED physician: *The diagnosis of gastroenteritis/acute intestinal infectious process is at the discretion of the emergency department supervising physician. Alternative terminologies that reflect a similar diagnosis are acceptable provided they meet all other eligibility criteria. Examples include: viral illness, diarrhea, vomiting, upper respiratory infection, post-infectious gastroenteritis, antibiotic associated diarrhea, toddlers diarrhea, viral infection, enteritis, viremia, fever, and bronchiolitis.*
4. Child/youth aged 6 months to 17.99 years.
5. Presence of ≥ 3 episodes of vomiting in the preceding 24 hour period (in the 24 hours preceding the screening process performed by the research team).
6. Duration of vomiting and/or diarrheal symptoms < 72 hours (*a 24 hour vomit and diarrhea free interval denotes a separate illness and only continuous days since the last 24 hour vomit and diarrhea free period are included*).
7. A minimum of 1 episode of vomiting within 6 hours of the screening process performed by the research team (time of approach and screening to be recorded): Date of time of assessment of eligibility for this study.
8. A minimum of 1 dose of ondansetron (oral or intravenous) provided during the current emergency department visit.

*Due to the nature of the illness being studied and the fast paced environment of the Emergency Department, preliminary screening may occur prior to obtaining a final diagnosis and/or an order for ondansetron.*

### 5.2 EXCLUSION CRITERIA

Research staff will ensure selection of participants is fair and equitable in accordance with Article 4.1 of the Tri Council Policy Statement: *"Researchers shall not exclude individuals from the opportunity to participate in research on the basis of attributes such as culture, language, religion, race, disability, sexual orientation, ethnicity, linguistic proficiency, gender or age, unless there is a valid reason for the exclusion"*

In this study, language barrier may be listed as an exclusion criteria due to the amount of communication needed for the follow-up portion of the study and the potential risks associated with administration of ondansetron. If the participant is unable to speak English or French, and the study team is unable to find an individual who speaks the participant's language (family member, hospital translator, etc.), they will not be consented or enrolled in the study. Similarly, because communication is a key piece of the study, if a person is unable to provide follow-up and comprehend the informed consent form they will not be able to participate in the study.

Individuals who meet **any** of the following criteria will be excluded from participation in this study:

1. Bilious (having a green or bright yellow colour, indicating larger amounts of bile in the stomach) or bloody vomit during current illness: *This may indicate an alternate diagnosis.*
2. Known hypersensitivity to ondansetron or any serotonin receptor antagonist (e.g. palonosetron, dolasetron, granisetron).
3. Known allergic reaction to components of ondansetron (*citric acid, sodium benzoate, sodium citrate dihydrate, and strawberry flavor, sorbitol*) or the placebo medication (*methylparaben, glycerin, citric acid, potassium sorbate, sorbitol, strawberry flavor*)
4. History or family history (first degree relative) of prolonged QT syndrome
5. Presence of complex congenital heart disease
6. History or family history (first degree relative) of cardiac arrhythmia
7. Concomitant use of (within the past 48 hours OR being prescribed) any of the following – *For a full list of possible medications in the following categories, please references the TMOP:*
  - a) QTc prolonging medications (e.g. methadone, anti-depressants, antiarrhythmics)
  - b) Medications known to cause torsades de pointes (e.g. macrolide antibiotics, apo morphine (*a morphine decomposition product that does not contain morphine or it's skeleton, nor does it bind to opioid receptors; acts as an antagonist of 5-HT2 and  $\alpha$ -adrenergic receptors with high affinity*)
  - c) Medications that cause electrolyte abnormalities (e.g. high dose corticosteroids, diuretics)
  - d) Serotonergic or neuroleptic medications: *Risk of serotonin syndrome or neuroleptic malignant syndrome* (e.g. triptans, SSRIs, SNRIs, fentanyl, MAOIs, lithium)
  - e) Any 5-HT3 receptor antagonist excluding ondansetron: *Cross reactivity has been reported between different 5-HT3 antagonists*
8. Unable to complete follow-up due to travel, no telephone or internet availability, or a language barrier beyond reasonable accommodation.
9. Previously enrolled in this study.
10. History or family history (first degree relative) of G6PD deficiency: *Due to the small amount of quinine present in the placebo compound which in theory can trigger a hemolytic crisis.*

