### 6.2.2 FORMULATION, APPEARANCE, PACKAGING, AND LABELING

#### **Active Study Medication:**

**Product:** Ondansetron Oral Solution, USP

**Manufacturer:** Sandoz Canada, a division of Novartis or JAMP Pharmaceuticals, Canada (based on availability)

| Summary Product Information – Active |                                                                         |                                                                                                               |
|--------------------------------------|-------------------------------------------------------------------------|---------------------------------------------------------------------------------------------------------------|
| Route of Administration              | Dosage Form / Strength                                                  | Nonmedicinal Ingredients                                                                                      |
| Oral                                 | oral solution/
4 mg/5 mL ondansetron (as
hydrochloride dihydrate) | citric acid, sodium benzoate, sodium
citrate dihydrate, sorbitol, strawberry
flavour (contains ethanol) |

Ondansetron hydrochloride is a selective antagonist of the serotonin receptor subtype, 5-HT3. Its precise mode of action in the control of nausea and vomiting is not known.

**Pharmacodynamics:** In vitro metabolism studies have shown that ondansetron is a substrate for human hepatic cytochrome P450 enzymes, including CYP1A2, CYP2D6 and CYP3A4. In terms of overall ondansetron turnover, CYP3A4 played the predominant role. Because of the multiplicity of metabolic enzymes capable of metabolizing ondansetron, it is likely that inhibition or loss of one enzyme (e.g. CYP2D6 enzyme deficiency) will be compensated by others and will result in little change in overall rates of ondansetron clearance.

**Pharmacokinetics:** Pharmacokinetic studies in human volunteers showed peak plasma levels of 20-30 ng/mL at around 1½ hours after an 8 mg oral dose of ondansetron. An 8 mg infusion of ondansetron resulted in peak

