### **Study Comparator**

**Product:** Placebo Oral Solution

**Manufacturer/Supplier:** Formulation provided by the University of Manitoba, College of Pharmacy. Compounding completed locally at participating site pharmacies.

| Summary Product Information – Comparator |                                     |                                                                                                                                                 |
|------------------------------------------|-------------------------------------|-------------------------------------------------------------------------------------------------------------------------------------------------|
| Route of Administration                  | Dosage Form / Strength              | Nonmedicinal Ingredients                                                                                                                        |
| Oral                                     | oral placebo solution/
4 mg/5 mL | methylparaben, glycerin, citric acid,
potassium sorbate, sorbitol,
strawberry flavour, quinine
concentrate (purified or sterile water) |

A Health Canada CTA is not required for this study however compliance with the Food and Drug Act will be maintained. Per Health Canada's Food and Drug Act (C.05.011), the study drugs and placebos will bear a label that sets out the following information in both official languages:

- (a) a statement indicating that the drug is an investigational drug to be used only by a qualified investigator;
- (b) the name, number or identifying mark of the drug;
- (c) the expiration date of the drug;
- (d) the recommended storage conditions for the drug;
- (e) the lot number of the drug;
- (f) the name and address of the sponsor; and
- (g) the protocol code or identification;

In addition, the following records will be maintained pertaining to the study drug:

- A copy of all versions of the product monograph and investigator brochure, if applicable
- Records respecting the shipment, receipt, position, return, and destruction of the drug

*For more information regarding formulation and stability, please reference the Zofran® and Ondansetron Oral Solution 4mg/5mL product monographs (Appendix A and B).*

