## 8 STUDY ASSESSMENTS AND PROCEDURES

### 8.1 EFFICACY ASSESSMENTS

Primary and secondary endpoints will be determined by the outcome measures. Assessments performed will support the outcome measures listed in Section 3.0 Objectives and Endpoints.

**Screening:** Participants presenting to the ED of a participating institution will be screened for eligibility using the eligibility criteria listed in sections 5.1 and 5.2 by a trained research team member. The research team member will ask the caregiver questions related to the patient's medical history and current medications that may be contraindicated. Inclusion/exclusion criteria will be determined based on caregiver report of patient's medical history and the details of their current illness. This information will be confirmed with the treating physician to ensure accuracy of reported information and medical oversight. In addition to the patient's medical history, eligibility depends on the treating physician ordering at least 1 dose of ondansetron while the patient is still in the ED, as well as the patient's ED diagnosis. This information will be confirmed using physician or nursing orders and the patient's ED medical chart by the research team member. Permission to access the patient's chart for screening purposes will be obtained from the caregiver/legally authorized individual, in accordance with provincial access to health information legislation.

**Enrollment/Baseline Assessments (outcome assessment):** A baseline questionnaire will be performed to obtain information supporting the study's outcome measures (e.g. *current medical history, duration and frequency of vomiting, presence of fever, duration and frequency of diarrhea, satisfaction scale, etc.*).

In addition to the questionnaire listed above, the trained research team member will obtain the participant's heart rate (HR) and respiratory rate (RR) at the Enrollment/Baseline visit. The triage temperature and weight will be obtained from the ED medical record. To obtain a baseline understanding of the participant's health and medical condition, a basic review of systems and concomitant medications will also be performed.

**Follow-up:** Outcome measure end-point data will be obtained using follow-up questionnaires performed 24, 48, and 168 hours (7 days) after the Baseline/Enrollment visit Time 0 (Consent date and time) by research study staff. Questions will be asked related to the following:

- Frequency and duration of vomiting

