## 8.2 SAFETY AND OTHER ASSESSMENTS

The following assessments will be performed to ensure the safety of patients as they participate in the study and to assess safety endpoints as described below:

- Frequency and maximal number of diarrheal episodes during the 48 hours following randomization
- Palpitations
- Syncope
- Chest pain

- Arrhythmias
- Serious Adverse Events

Please reference Section 1.3 SoA for a list of all study events/visits.

If caregivers report any symptoms of concern to the research team (palpitations, arrhythmias, syncope, etc.) or are concerned about their child's health, they will be advised to follow up with their health care provider or seek immediate medical attention at the nearest hospital. Caregivers will be provided with a list of possible reasons to seek medical care and a disclaimer regarding symptoms of concern and the required action will be included on all follow-up questionnaires.

**Screening:** A detailed review of the patient's medical history related to the eligibility criteria (e.g. history of prolonged QT syndrome, currently taking apo morphine, etc.) will be performed by the qualified research team member with the caregiver. The information will then be confirmed by the treating physician to comply with medical oversight and ensure patient safety. We will rely on caregiver report of current medications and the medical history of the patient to assess eligibility.

**Baseline/Enrollment Visit – Review of Systems:** After the patient is deemed eligible and has consented to participate in the study, a review of systems will be performed by the qualified research team member to obtain baseline health information prior to starting the study intervention. The research team member will ask the caregiver/participant questions related to the participant's general health by system (e.g. cardiovascular, respiratory, musculoskeletal, etc.). This allows the research team to more accurately measure any new symptoms or conditions that occur after enrollment in the study. During the review of systems, the research team will also ask the caregiver/participant if they are currently taking any medications or supplements. This information will be recorded on study case report forms. This process will take place after the clinical dose of ondansetron is administered however it must be completed prior to the participant taking the first dose of study medication.

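### The placebo ingredient list in exclusion criterion 3 leaves out quinine, which Section 6.2.2 and criterion 10 both say the placebo contains

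*Combined protocol and SAP*

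**What the plan says.** Section 5.2, criterion 3, opens with "Known allergic reaction to components of ondansetron" and extends the exclusion to the placebo. Each product is followed by a bracketed ingredient list. For the placebo the list reads "methylparaben, glycerin, citric acid, potassium sorbate, sorbitol, strawberry flavor". Criterion 2, immediately above, marks its own list as illustrative: "e.g. palonosetron, dolasetron, granisetron". Criterion 3 has no such marker.

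The comparator table in Section 6.2.2 continues past the flavouring: "strawberry flavour, quinine" concentrate, with water as the vehicle. Criterion 10 of Section 5.2 excludes a personal or first-degree family history of G6PD deficiency, and gives as its reason "Due to the small amount of quinine present in the placebo compound".

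On how eligibility is established, Section 8.2 states "We will rely on caregiver report of current medications and the medical history of the patient to assess eligibility". Section 8.1 adds a second step: "This information will be confirmed with the treating physician to ensure accuracy of reported information and medical oversight".

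**The concern.** Two parts of the same protocol give different contents for the placebo, and the shorter list is the one inside an operative safety criterion. The missing ingredient is also the only placebo component for which the protocol itself names a specific hazard.

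Criterion 10 does not close the gap. It deals with haemolysis in G6PD deficiency, which is a different mechanism from allergy and leads to a different question to the caregiver.

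What is at stake is the safety of an individual child in a rare case. Eligibility depends first on what caregivers report when asked, so an ingredient that nobody names is less likely to bring out a relevant history. Doses are given at home, where no clinician would see a reaction. Section 8.3.5 also lists rash among the disease-related events that fall outside standard adverse event reporting, so a reaction showing only as a rash might not be reported by that route.

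**Working it through.** The main check is a comparison of two lists. The water vehicle is left out.

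| Placebo ingredient | Section 5.2, criterion 3 | Section 6.2.2, comparator table |
|---|---|---|
| Methylparaben | listed | listed |
| Glycerin | listed | listed |
| Citric acid | listed | listed |
| Potassium sorbate | listed | listed |
| Sorbitol | listed | listed |
| Strawberry flavouring | listed | listed |
| Quinine concentrate | **absent** | listed |
| Count | 6 | 7 |

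The difference is 7 − 6 = 1, and the missing ingredient is quinine. Criterion 10 states independently that the placebo contains quinine, so the table entry is not a stray one.

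The active product is not a clean comparison. Criterion 3 names all five ingredients in the active table, but that table also notes ethanol within the strawberry flavouring, which criterion 3 does not mention. The argument therefore does not rely on the active list being complete.

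For scale, Section 1.1 gives 1030 participants and Section 6.3 gives 1:1 allocation:

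- Placebo arm: 1030 / 2 = 515.
- The documents give no prevalence of known quinine allergy. An assumed range of 1 in 100,000 to 1 in 1,000 is used.
- Lower end: 515 × 0.00001 = 0.00515, about 0.005 children.
- Upper end: 515 × 0.001 = 0.515, about 0.5 children.

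These are expected numbers before any screening. For harm to follow, several things must all happen: the known allergy is missed by both caregiver and treating physician, the child is allocated placebo, and at least one dose is given. Section 6.4 allows a caregiver to give none.

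**The case against.** The strongest reply is that no exclusion is missing. The rule covers components of the placebo, the ingredients sit in brackets after it, and a child with a known quinine allergy is ineligible as the criterion is written. That is correct, and it limits the point to an incomplete list.

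It can also be said that the misreading is conjecture. Nothing supplied shows that staff screen from the bracketed list. The screening form and the trial manual of procedures were not provided, and they may already ask about quinine. Criterion 10, in the same list, tells the screener that quinine is present, and the treating physician confirms the history. All of this lowers the chance of a miss. It does not remove the mismatch, because criterion 10 prompts a question about G6PD deficiency and not about allergy.

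The prevalence range has no basis in the documents. That is true; it serves only to show that the expected number is below one child at either end.

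Finally, version 4.0 added a second placebo formulation to match the generic product, while Section 6.2.2 has a single comparator table. The formulations are in Appendices C and D, which were not available. Adding quinine is supported by the table and by criterion 10, but whether it makes the list complete for both formulations could not be checked.

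**Conclusion.** The point holds as a minor inconsistency in a safety criterion. Criterion 3 lists six of the seven non-water placebo ingredients in Section 6.2.2, omits quinine, and does not present its list as examples. The mismatch itself is certain from the text.

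The practical risk is low: fewer than one placebo-allocated child expected with a known quinine allergy across the assumed range, with screening still to come. There is no effect on sample size, power, type I error or the primary analysis. Whether staff already ask about quinine is unknown. This is a change worth considering, and it does not call the design into question.

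**What to change.** Add quinine to the placebo ingredients in criterion 3, and add it to the allergy question on the screening form if that form does not already name it. When making the edit, check the list against Appendices C and D so that it covers both placebo formulations.

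The cost is one word in the protocol and at most one item on a form. Under the Statement of Compliance, an amendment needs research ethics board review and approval before it is implemented, so the change can go with the next amendment. No analysis or sample size work is needed.
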